**9.5. Incentives**

Per test session subjects will receive a financial compensation of 75 euro, which is 300 euro in total after completion of the study. Possible travel expenses will be declared.

## **10. ADMINISTRATIVE ASPECTS AND PUBLICATION**

### **10.1. Handling and storage of data and documents**

Subjects' personal information will be confidentially handled during the study, according to the Dutch Personal Data Protection Act (Wet bescherming persoonsgegevens; Wbp). Results will be linked to the intervention and not to individual subjects. Subject numbers (e.g. number 1) in combination with treatment codes (100%control, code A; 75%Control, code B, 100%CAPS, code C; 75%CAPS, code D) will be used throughout the study. Only the researcher is familiar with subject information, so privacy of personal information is guaranteed. If desirable, subjects will be informed about their personal study results at the end of the study. Collected body material (urine) will be destroyed after publication of the results. Personal data will be kept for a period of 15 year, which is the legal time to keep medical data. Hereafter the data will be destroyed.

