### 3. STUDY DESIGN

#### 3.1. Study design

The study will be conducted in a double-blind crossover design with four randomly sequenced experimental conditions. This 2x2 latin square design will be applied to give a complete picture of the combined effects of capsaicin supplementation and energy balance.

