#### 3.2. Intervention

Subjects will stay for four conditions in a respiration chamber for 36h, twice receiving an energy-balanced (100 En%) diet and twice an energy-restricted (75 En%) diet, both with and without added capsaicin (100%Control, 75%Control, 100%CAPS, 75%CAPS). The four test sessions will be conducted four weeks apart to prevent possible treatment-induced effects and to take eventual effects of menstrual cycle phase on energy intake and energy expenditure in women into account.

Two days prior to each test session subjects will be provided with a diet at home, in energy balance and with the same macronutrient composition as they will receive during the test sessions. On each of the four test days subjects arrive at the University after an overnight fast at 8:00h, whereafter they enter the respiration chamber at 8:30h. Energy expenditure, substrate oxidation and activity level will be continuously measured from 8:30h to 20:30h on the next day. Breakfast will be provided at 8:30h and will consist of wholegrain bread with low-fat margarine, liver paste and strawberry jam, and chocolate milk. At 13:30h subjects will receive lunch, which will consist of wholegrain bread with low-fat margarine, liver paste and meatloaf, ginger cake, low-fat milk, apple and raisin biscuits. Dinner at 18:30h will consist of mixed salad with dressing, vegetable lasagne, low-fat yoghurt and low-fat milk. As part of each meal subjects will consume tomato juice (100%Control, 75%Control conditions) or tomato juice with added capsaicin (100%CAPS, 75%CAPS conditions). Subjects will be instructed to go to sleep around 23:30h. The next morning, subjects will be waked at 7:30h. Thereafter, the same protocol as during the previous day will be followed, until dinner. At 18:30h the subjects will receive an *ad libitum* meal, consisting of iceberg lettuce with cucumber, tomato and dressing, macaroni Bolognese, a dessert and orange juice.

Appetite profile will be measured using anchored 100-mm visual analogue scales (VAS). These questionnaires will be completed every waking hour, and before and after every meal on feelings of hunger, fullness, appetite, satiety, thirst, prospective food consumption, and desire to eat. Mood and anxiety levels will be measured by Profile of Mood State (POMS) (22) and State-trait Anxiety Inventory (STAI) (23) questionnaires at the same time points.

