## 5. TREATMENT OF SUBJECTS

### 5.1. Investigational product/treatment

Red pepper from the *Capsicum frutescens* L and *Capsicum annuum* L (McCormick; origin, India; sample ID, EC88746100) will be used as source for capsaicin. This specific form of red pepper has previously been used in a study of Ludy et al, investigating the effects of red pepper on thermogenesis and appetite (11). The product contains nordihydrocapsaicin (NDC; 930 Scoville heat units (SHU)), CAPS (26380 SHU) and dihydrocapsaicin (DHC; 11740 SHU), making a total amount of CAPS of 39050 SHU. Capsaicin will be given at a dose of 80.000 SHU, corresponding to an amount of 5.12 mg capsaicin (2.05 g of red pepper), with every meal. This dosage is based upon the maximal dosage given in previous studies (8, 19, 20). Divided over three meals, a daily total dose of 15.36 mg CAPS will be consumed by the subjects. Subjects will receive the capsaicin for two subsequent days. Because it is suggested that the maximum tolerable dose (about 6.0 g/L) of red pepper is necessary to have a suppressive effect of red pepper on fat intake (27) and that hedonics may be reduced when the concentration of red pepper is higher than 6.0 g/L of red pepper (10), the tomato juice with capsaicin that we chose to offer during this experiment contains 6.0 g/L of red pepper. Per meal subjects will consume 2.05 g of red pepper dissolved in 250 mL tomato juice.

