### 6.2. Randomisation, blinding and treatment allocation

The study will be conducted in a double-blinded crossover design with four randomly sequenced experimental conditions.

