All food items, including capsaicin, are suitable for humans. The commercial available food products will be bought by the researchers and immediately after purchase transported by car to the University. Refrigerated products will be taken in deepfreeze bags. After arrival at the University the refrigerated products will be stored immediately at either a 4°C fridge or a -20°C freezer in the research kitchen from the Department of Human Biology. This research kitchen meets all the criteria for safe and proper use of food items in human clinical studies. Capsaicin will be processed, handled, packaged and transported by McCormick, as described in the HACCP-analysis. After arrival at the University the product will be stored in a locked food depot in the research kitchen. Capsaicin will be stored for a maximum period of one year, which corresponds to the maximum duration of the study and will not exceed the expiration date of the product. A certified dietician controls the storage of the products. Before preparation of the meals the dietician will check the expiration dates of the food items. Expired food items will immediately be removed. All food items will be prepared in the research kitchen from the Department of Human Biology by a certified dietician just before they are offered to the subjects. Fresh food items will be used every day, and food items will be stored for a maximum period of one week. Capsaicin will be weighed and mixed with the tomato juice by the dietician just before it is offered to the subjects. Addition of capsaicin will not largely influence the taste of the tomato juice, although the juice will be slightly spicier. Further information can be found in the guideline 'MEC azM/UM for preparation, delivery and administration of products for human usage in clinical studies'.

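### The trial is labelled double-blind, but its single printed code key masks nothing from staff who hold the protocol, and subject masking to capsaicin cannot be assumed

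*Protocol*

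**What the plan says.** **Label.** Protocol section 3.1: "The study will be conducted in a double-blind crossover design with four randomly sequenced experimental conditions". Section 6.2, which covers randomisation, blinding and allocation, is one sentence: "The study will be conducted in a double-blinded crossover design with four randomly sequenced experimental conditions". Neither section says who is masked, how the drinks are matched or who holds the code.

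**Codes.** Section 10.1 pairs each subject number with a treatment code and adds that "treatment codes (100%control, code A; 75%Control, code B, 100%CAPS, code C; 75%CAPS, code D) will be used throughout the study". This is the only coding rule in the protocol.

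**Drinks.** Section 3.2: "As part of each meal subjects will consume tomato juice (100%Control, 75%Control conditions) or tomato juice with added capsaicin". Section 5.1 puts the maximum tolerable strength at about 6.0 g/L, warns that "hedonics may be reduced when the concentration of red pepper is higher than 6.0 g/L of red pepper", and says that "the tomato juice with capsaicin that we chose to offer during this experiment contains 6.0 g/L of red pepper". It then describes the serving: "Per meal subjects will consume 2.05 g of red pepper dissolved in 250 mL tomato juice". Section 9.3 says: "Addition of capsaicin will not largely influence the taste of the tomato juice, although the juice will be slightly spicier". The same section has the dietician weigh the capsaicin and mix it into the juice.

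**The concern.** Double-blind is a claim about the design that readers use to judge how far expectation could have shaped the results. Here the protocol's own coding rule works against that claim on the staff side, and its own description of the drinks puts it in doubt on the subject side.

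The outcomes at stake are not peripheral. The primary objective in section 2 names appetite profile and ad libitum intake beside energy expenditure and substrate oxidation. Section 6.1.2 lists VAS, POMS, STAI and ad libitum intake as secondary endpoints. All of these are self-reported or behavioural, so a subject's belief about the drink could move them. A reader told that the trial was double-blind would give them more weight than the procedures support.

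**Working it through.** The staff side needs no calculation. The subject side needs a little arithmetic on the drink and the meals.

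**1. What the code conceals.** A code masks only if its reader does not know what it stands for. Section 10.1 fixes A = 100%Control, B = 75%Control, C = 100%CAPS and D = 75%CAPS for everyone. One record read against the protocol gives the condition. The key covers 16 subjects x 4 sessions = 64 planned sessions. That is the reach of the key and does not measure bias.

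**2. Staff steps that masking would protect.**
- Section 6.3.2 derives resting metabolic rate from a regression of energy expenditure on radar output. DIT is RMR minus SMR, and AEE is 24h expenditure minus SMR minus DIT. These components are secondary.
- Section 6.3.6 has leftovers from the ad libitum dinner weighed by hand, by staff it does not name.
- Total 36h energy expenditure does not depend on the RMR regression. It comes from gas analysers whose samples are selected, stored and processed by computer.

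**3. The drink.** The stated strength is 6.0 g/L. The serving in the same section gives 2.05 g / 0.250 L = 8.2 g/L, and 8.2 / 6.0 = 1.37, so 37% higher. Conversely, 250 mL at 6.0 g/L holds 6.0 x 0.250 = 1.5 g, and 2.05 g at 6.0 g/L needs 2.05 / 6.0 = 0.342 L, about 342 mL. The stated figure is not reproduced. For masking it makes no difference which applies: the comparison is juice with no red pepper against juice at or above the level called maximum tolerable.

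**4. Opportunity to compare.** Juice accompanies every meal. Before the ad libitum dinner there are three meals on day 1 and two on day 2, so at least five servings per session. Over two capsaicin and two control sessions, each subject has at least 10 servings of each juice.

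**5. Meal size.** Section 6.3.6 sets 75% or 100% of energy requirement. It prints one test menu (Table 2) and no 75% menu. If every item except the 250 g of juice were cut by a quarter (an assumption), total mass would fall as follows:

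| Meal | Other food (g) | With juice (g) | Cut (g) | Fall in total |
|---|---|---|---|---|
| Breakfast | 310 | 560 | 77.5 | 14% |
| Lunch | 625 | 875 | 156 | 18% |
| Dinner | 1152 | 1402 | 288 | 21% |

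The contrast used for the sample size in section 4.4 is 75%CAPS against 75%Control. Energy level is the same in both, so meal size cannot separate them.

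**6. What analysts will see anyway.** Section 8.1 calls for energy and macronutrient intake and balance. Those data show the energy level whatever the code, so better coding can mask capsaicin but not energy restriction.

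**The case against.** The best defence has four parts.

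- **Section 10.1 is about privacy.** It pairs numbers with codes to protect identity and does not say which staff see coded records or have the key to hand. This limits the claim: the key can be read by anyone holding the protocol, but the document does not show that every handler will read it. The code still cannot provide masking, and no other coding is described.
- **The taste difference is described as small.** Section 9.3 says the taste is not largely affected and the juice only slightly spicier, and section 5.1 treats 6.0 g/L as a threshold above which liking may fall. This stands as a limit. That subjects notice is a likely inference, and no check of it is planned.
- **The primary endpoint is instrument-measured.** This stands. Activity is one component of total expenditure and subjects spend their time in the chamber largely as they like, so some route for expectation exists. The document gives neither its size nor its direction.
- **Blinding details may sit in another document.** They may, but the point rests on what sections 3.1, 6.2 and 10.1 state, not on what they leave out.

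A reader might go further in three ways that the documents do not support.

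- **That subject blinding is absent.** Nothing in the protocol establishes detection.
- **That the 75% meals are a quarter smaller and so reveal the condition.** The protocol fixes energy, not portion mass. Even the proportional-cut assumption gives falls of 14% to 21%, and meal size carries no information about capsaicin.
- **That the juice is really 8.2 g/L.** Section 5.1 contradicts itself, and this review cannot say which figure applies.

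**Conclusion.** The point holds for the label and the code. An unqualified double-blind claim is inconsistent with a constant, printed key, because staff who hold the protocol can decode any coded record. This needs no assumption about perception. It assumes only that the codes appear on the records as section 10.1 says.

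On the subject side the conclusion is weaker. Masking to capsaicin is doubtful and should not be assumed, given a plain comparator, a strength called maximum tolerable and repeated within-subject exposure to both juices.

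The size of any bias cannot be derived from the protocol. The exposure is mainly in VAS, POMS, STAI and ad libitum intake, and less in 36h energy expenditure. The sample size and the design itself are unaffected. The correction should be made because it costs little and the present label overstates protection for outcomes named in the primary objective.

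**What to change.** 1. In section 10.1, replace the constant A-D key with random codes generated per subject and session. The dietician who mixes the juice, and so already knows its content, holds the list until data lock. Staff who process and analyse the data are then masked to capsaicin up to that point.
2. In sections 3.1 and 6.2, replace the unqualified label with a statement of who is masked to what. It should say that data staff are masked to capsaicin but not to energy level, which the intake and balance data show; that the dietician is not masked; and that subject masking to capsaicin cannot be assumed. It should also name who weighs the ad libitum leftovers and whether that person is masked.
3. Interpret VAS, POMS, STAI and ad libitum intake with that limit stated.
4. As a separate matter, reconcile the two descriptions of juice strength in section 5.1 (6.0 g/L, and 2.05 g in 250 mL).

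Items 1 to 3 cost a new code list, wording in three sections and a less favourable design label. They change no visit, measurement or sample size.

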### **10.2. Amendments**

Amendments are changes made to the research after a favourable opinion by the accredited METC has been given. All amendments will be notified to the METC that gave a favourable opinion.

### **10.3. Annual progress report**

The investigator will submit a summary of the progress of the trial to the accredited METC once a year. Information will be provided on the date of inclusion of the first subject, numbers of subjects included and numbers of subjects that have completed the trial, serious adverse events/ serious adverse reactions, other problems, and amendments.

### **10.4. End of study report**

The investigator will notify the accredited METC of the end of the study within a period of 8 weeks. The end of the study is defined as the last patient's last visit.

In case the study is ended prematurely, the investigator will notify the accredited METC, including the reasons for the premature termination.

Within one year after the end of the study, the investigator will submit a final study report with the results of the study, including any publications/abstracts of the study, to the accredited METC.

### **10.5. Public disclosure and publication policy**

The 'CCMO Statement on publication policy' will be followed to publish research results after the end of the study.

